### Data Analysis

#### Power Analyses

The power analysis conducted to estimate the sample size required to test the hypotheses of this study used the procedures suggested by Cohen [73] for estimating statistical significance. That is, what is the sample size required to detect an increase in the variance explained due to the inclusion of the personalized feedback pamphlet intervention into the model (Hypothesis 1)? Based on pilot study results, a 1% increase in explained variance can be expected (a small effect size of f = 0.10; note – corresponded to a reduction of two drinks per week in the pilot study). Following the convention that studies should be designed to have a statistical power of at least 80%, and that hypotheses be tested at the .05 level of significance, SamplePower 1.0 [74] was used to estimate the required sample size. These specifications resulted in a final sample (required after attrition) of N = 390 in each condition (N = 1170 total). Given that the inclusion of perceived risk as a moderator resulted in an increase in explained variance of 9% (also in the pilot test), this same sample size would result in a power of better than 99% to test for the mediator and moderator hypotheses (assuming a similar effect size). Results presented by Neighbors and colleagues [44] found similar effect sizes for the mediator hypothesis regarding perceived drinking norms and the moderator hypothesis regarding drinking for social reasons, indicating that the proposed sample size will be adequate to test these hypotheses as well.

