Although Structural Equation Modeling [75], the analysis method to be used, allows for the sophisticated treatment of missing data, it is still important to assure an adequate number of respondents are followed-up. Based on previous experience [76], it is estimated that 80% of respondents will be followed-up on the six-month follow-up. This means that about 1830 respondents who agree to the follow-up will need to be recruited on the baseline survey in order to account for respondent attrition. We are assuming a worst-case scenario of an 80% follow-up rate on each of the three-month and six-month follow-up interviews but that the 20% lost on each follow-up survey will be different respondents. Thus, to obtain 1170 respondents with complete follow-up data, a follow-up rate of 80% × 80% = 64% is assumed. Given that previous research [77] has indicated that 75% of problem drinkers will agree to be followed-up, the baseline survey will need to include 2440 respondents who are problem drinkers (AUDIT score of 8 or more). As 20% of the baseline sample will be problem drinkers, the full baseline survey will need to screen 12200 respondents who consume alcohol at least once per month (based on previous experience, 20% of monthly alcohol drinkers have an AUDIT score of 8 or more). This will allow a final sample size of 1170 problem drinkers participating in the six-month follow-up. In summary, from 12,200 respondents interviewed at baseline 20% (n = 2440) will be problem drinkers, 75% of whom (n = 1830) will agree to participate in the follow-up interviews, and an 80% follow-up rate for each follow-up survey will give total data for 1170 respondents.

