#### Analysis Plan

The analysis plan will follow the description of the use of Structural Equation Modeling (SEM) [75] for the analyses of experimental studies provided by Neighbors et al. [44] and by Russell et al. [78]. SEM with full information maximum likelihood will be used. Effect sizes will be reported [79,80].

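### The attrition paragraph's loss pattern, its 64% completeness and its 1170 at six months do not fit together

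*Protocol article*

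**What the plan says.** The Power Analyses section of the protocol article first sets a requirement of 390 per condition, 1170 in all, after attrition. It then works back to the number to recruit.

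- It gives an expected rate from past experience: "it is estimated that 80% of respondents will be followed-up on the six-month follow-up". The next sentence presents about 1830 recruited as following from this.
- It describes a worst case of 80% follow-up at each of the three-month and six-month interviews, in which "the 20% lost on each follow-up survey will be different respondents".
- From this it concludes that, for complete follow-up data on 1170, "a follow-up rate of 80% × 80% = 64% is assumed".
- After the screening figures (2440 problem drinkers, 12,200 screened) it says: "This will allow a final sample size of 1170 problem drinkers participating in the six-month follow-up". The closing summary describes the same 1170 as those with total data.

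The Analysis Plan section adds: "SEM with full information maximum likelihood will be used".

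**The concern.** Three statements have to hold together: who is lost at each wave, what share has both follow-ups, and how many are seen at six months. Multiplying 80% by 80% allows some people to miss both interviews, yet the sentence before it says that the two lost groups are different people. One number, 1170, is also used for two quantities that differ whenever anyone misses only the three-month interview: respondents with both follow-ups, and respondents seen at six months.

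This paragraph is the only stated basis for the recruitment target and for judging retention later. As written, 1170 seen at six months looks like meeting the plan, although it would be 64% retention against a stated 80%. The figure offered as the worst case is also not the worst case for two 20% losses from the recruited cohort.

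**Working it through.** **Inputs, all from Power Analyses:** 1170 required (390 × 3); 80% followed up at each wave; 1830 recruited; 75% agreeing to follow-up; 20% of those screened being problem drinkers. For power: "hypotheses be tested at the .05 level of significance" (sidedness is not given; two-sided is assumed), the convention that "studies should be designed to have a statistical power of at least 80" per cent, and "a 1% increase in explained variance can be expected (a small effect size of f = 0.10".

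**1. The plan's own chain reproduces.**
- 1170 / 0.64 = 1828, stated as about 1830. Forward, 1830 × 0.64 = 1171.
- 1830 / 0.75 = 2440, and 2440 / 0.20 = 12,200.
- For two equal groups d = 2f = 0.20. A two-sided comparison of two means with 80% power needs 393 per arm, close to the stated 390.

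**2. What each loss pattern implies for 1830 recruited.**

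| Loss pattern | Both follow-ups | Seen at six months |
|---|---|---|
| Independent, 20% of all recruited at each wave | 0.8 × 0.8 = 64%, 1171 | 80%, 1464 |
| Different people, 20% of all recruited at each wave | 1 − 0.2 − 0.2 = 60%, 1098 | 80%, 1464 |
| Sequential, then 20% of those remaining | 0.8 × 0.8 = 64%, 1171 | 64%, 1171 |

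- Independent loss implies 0.2 × 0.2 = 4% missed at both waves, or 1830 × 0.04 = about 73 people. That is the overlap which the wording on different respondents excludes.
- Different people, with both losses taken from the recruited cohort, contradicts 64%.
- Sequential loss fits different respondents, 64% and 1170 at six months, but contradicts 80% followed up at six months.

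No row satisfies every statement.

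**3. Power in a simple two-arm comparison**, Φ(d√(n/2) − 1.96) with d = 0.20:
- n = 366 (1098 / 3): 0.20 × √183 = 2.706, less 1.96 = 0.746, giving 77.2%.
- n = 390: 0.20 × √195 = 2.793, less 1.96 = 0.833, giving 79.8%.
- n = 488 (1464 / 3): 0.20 × √244 = 3.124, less 1.96 = 1.164, giving 87.8%.

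The t distribution gives 77.1%, 79.7% and 87.7%. The complete-case difference between 366 and 390 per arm is 79.8 − 77.2 = 2.6 points.

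**4. Who contributes under FIML.** With different people lost, 1464 are seen at three months and 1464 at six. The number seen at least once is 1464 + 1464 − 1098 = 1830. So 1098 is not the analysed number, and neither is 1464.

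**The case against.** The best defence is that the arithmetic is sound and only one phrase is loose. Every multiplication and division is correct. Read sequentially, the two lost groups are indeed different people, completeness is 64%, and about 1171 take part at six months. The section does not state the denominator of the second 80%. The 80% from past experience could also be an expectation that sits beside a more cautious planning case, which would explain why 1170 rather than 1464 is named at six months.

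Part of this stands. The calculation steps are right, and 60% depends on taking both losses from everyone recruited. But the sequential reading puts six-month follow-up at 64%, while the section ties 1830 directly to its estimate of 80% at six months and repeats 80% as the rate for each interview. It moves the contradiction elsewhere without removing it.

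The defence is fully right on consequences. A reader might infer that the trial falls short of its required size under its own worst case, and that 1950 recruited, 2600 problem drinkers and 13,000 screened are needed (1170 / 0.60, then / 0.75, then / 0.20). That treats complete cases as the analysis set, whereas the plan specifies FIML, which also uses partly observed respondents. With different people lost at each wave, 488 per arm are seen at six months, above 390. A reader might also infer that six-month power is misstated. The document gives no separate six-month power; it sets a required size, and exceeding that size is a margin.

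**Conclusion.** The point holds as an internal inconsistency in stated figures, with a modest effect. If both 20% losses are shares of all recruited and fall on different people, 60% (1098; 366 per arm) have both follow-ups, and 64% (about 1171) belongs to independent losses. If the loss is sequential, 64% is correct and the 80% six-month rate is not. In the two readings where 80% are seen at six months, 1170 cannot be the number taking part then; it is 1464 (488 per arm).

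The complete-case cost is about 2.6 points of power, from about 80% to about 77%. This rests on d = 0.20, an assumed two-sided 0.05 test and a simple two-arm comparison, which approximates the explained-variance test the plan describes. It concerns only analyses needing both waves, such as Hypotheses 3 and 4, which pair change by three months with a six-month outcome. The plan claims better than 99% power for those on its own effect size, so the shortfall does not by itself threaten them. The documents do not support a conclusion that the Hypothesis 1 comparison at six months is undersized, or that recruitment must rise.

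**What to change.** Keep recruitment at 1830 and restate the paragraph in one of two ways.

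(a) Losses as shares of all recruited: describe 64% (about 1171) as the completeness expected under independent losses. Give 60% (1098; 366 per arm; complete-case power about 77%) as the worst case. Label 1170 as respondents with both follow-ups complete. State 1464 (488 per arm) as the number expected to be observed at six months, without calling it the FIML analysis size.

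(b) Sequential loss: say that the second 20% is taken from those who remain, keep 64% and 1170, and correct the six-month follow-up rate to 64% of those recruited.

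Under (a), add a sentence that partly observed respondents contribute under FIML, so the six-month comparison for Hypothesis 1 does not depend on the complete-case count. The cost is a few sentences and figures, with no change to recruitment, design or analysis method.

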#### Analysis Plan

The analysis plan will follow the description of the use of Structural Equation Modeling (SEM) [75] for the analyses of experimental studies provided by Neighbors et al. [44] and by Russell et al. [78]. SEM with full information maximum likelihood will be used. Effect sizes will be reported [79,80].

## Discussion

The primary goal of this project is to evaluate the efficacy of an ultra-brief self-help intervention for non-treatment seeking problem drinkers in the general population. One strength of the proposed study is that it merges population-based methods with a randomized controlled trial. Thus, a general population survey will be employed using a random digit dialing method in order to recruit a good cross-section of problem drinkers from the Toronto population. Respondents will be randomly assigned to condition, allowing for causal inference about any differences observed.

The information from the proposed trial may help illuminate effective ways of promoting change among problem drinkers who do not seek formal treatment. If the project finds support for the efficacy of a pamphlet-based feedback intervention, it would provide justification to substantially increase the accessibility of this self-help method for problem drinking. This would be accomplished by sending the pamphlet directly to the public in bulk mailing, to health care settings (treatment centers, hospitals, doctors' offices), and to other social services such as unemployment agencies and welfare departments. As problem drinking is common in all these settings, a research evaluated ultra-brief intervention made freely available to all those in need would help broaden the base of treatment for alcohol problems.

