## Background

The ratio of problem drinkers to those seriously dependent on alcohol is about 4:1 [1]. As Cahalan [2] has noted, "clinically defined alcoholics constitute only a relatively small proportion of those whose drinking creates significant problems for themselves and society" (p. 363). The majority of these problem drinkers, while being at risk for health problems and other psychosocial consequences [3], will never access any treatment services. (estimated ratio of treated to untreated problem drinkers ranges from 1:3 to 1:14 in Canada and the United States) [4-9]. Many individuals with drinking problems do not approach alcohol treatment facilities, often because of stigma, embarrassment or because they don't think of their drinking as a problem [5,10-12]. Further, when asked why they have not sought formal help or treatment, problem drinkers overwhelmingly indicate that they "want to change on their own" [10,13]. The present study proposes to test the effects of a self-change intervention that circumvents some of the barriers of traditional treatment by allowing problem drinkers to work on their alcohol problems on their own in private without approaching alcohol treatment facilities.

In 1990, the Institute of Medicine [1] recommended a broadening of the range of services for people with alcohol problems. Providing self-help interventions to individuals who have not accessed treatment services is one way to accomplish this important public health goal and ensure that a broader range of services is available. Although such interventions might only have a limited impact on an individual level, they can still be beneficial as part of a continuum of care for individuals unlikely to enter formal alcohol treatment programs [1,14,15]. Further, when viewed from a public health perspective [16], minimal interventions have the potential for a significant population-level impact as such interventions are low cost and can be provided to a large number of drinkers. Public health impact is typically conceptualized as the reach of the intervention X efficacy per unit cost [17]. The low cost and potential for broad reach of self-help interventions, coupled with the high base rate of the behavior suggests that such interventions can have a significant public health impact.

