### What is the principal research objective?

The principal research objective is to evaluate the efficacy of a pamphlet-based self-help intervention among problem drinkers in the general population. The development of an effective, research-based pamphlet of this type is important because of its potential for use in public health initiatives where low-cost and wide distribution are key considerations. In order to mimic the use of a personalized feedback pamphlet in a public health initiative, the pamphlet will be sent unaddressed to households rather than to specific individuals. In addition, because it is important to determine whether it is the content of the personalized feedback pamphlet or just the receipt of any pamphlet that leads to reductions in drinking, a control pamphlet condition will be included in the study.

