## Methods/design

### Aim

The proposed research will evaluate the efficacy of a pamphlet-based personalized feedback intervention for problem drinkers in the general population.

The hypotheses regarding the efficacy of the pamphlet-based intervention are:

Hypothesis 1: Respondents from households who receive the personalized feedback pamphlet-based intervention will display significantly improved drinking outcomes at three and six-month follow-ups as compared to respondents from households in the no intervention control condition.

Hypothesis 2: Respondents from households who receive the personalized feedback pamphlet-based intervention will display significantly improved drinking outcomes as compared to respondents from households who receive the control pamphlet.

In addition, two mediator hypotheses will be tested:

Hypothesis 3: Respondents who receive the intervention and reduce their estimates about how much others drink between baseline and three-month follow-up will display significantly improved drinking outcomes at six-month follow-up as compared to respondents who receive the intervention but experience no decrease in their perceived drinking norms.

Hypothesis 4: Respondents who receive the intervention and experience an increase in their perceived vulnerability to experience harm because of their alcohol consumption between baseline and three-month follow-up will display significantly improved drinking outcomes at six-month follow-up as compared to respondents who receive the intervention but experience no increase in their perceived risk.

Finally, two moderator hypotheses will be tested:

Hypothesis 5: The impact of the intervention will be greater among drinkers who believe that they are personally vulnerable to negative outcomes at baseline assessment, compared to drinkers who do not believe that they are personally 'at risk' before receiving the intervention.

Hypothesis 6: Respondents who drink for social reasons will be more likely to reduce their drinking as a result of the intervention as compared to respondents who do not drink for social reasons.

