#### Rationale for the choice of study design

Why do we believe that the proposed study design is the best for testing the impact of this personalized feedback pamphlet? The intent of this project is to evaluate an ultra-brief intervention for problem drinkers that can be used in public health initiatives. As such, it is important that the intervention pamphlet be evaluated in a setting that mimics how it will be used. Thus, the pamphlets will be sent addressed to the household rather than addressed to the respondents because public health initiatives are often non-specific in their target recipients. The proposed research design has the advantage of allowing the pamphlet to be sent to all households in the intervention condition, irrespective of whether any of the respondents are specifically interested in receiving self-help materials. In order to conduct a study where intervention materials are sent directly to the person by name, for ethical reasons the respondent must at least state that he or she is hypothetically interested in receiving such materials. A study in which materials are sent unsolicited to households has been judged ethical because receiving such materials unsolicited (and unaddressed to a specific individual) is not an unusual occurrence given that public health initiatives are ongoing in the Toronto metropolitan area. However, informed consent is given because all respondents are told about the possibility of their household receiving the pamphlet. Further, it is important to be able to send materials to all households because interest in self-help materials covaries with respondents' perceived risk. In the pilot study described above, 76% of problem drinkers who perceived no risk associated with their drinking were not interested in self-help materials. This group comprised 32% of all problem drinkers in the sample. Thus, although the proposed method reduces the power of the intervention because not all respondents will see the pamphlet, it is still the best design for our purposes because it allows recruiting some problem drinkers with no perceived risk regarding their alcohol consumption. Studying the reactions of problem drinkers who do not perceive any risk associated with their drinking to intervention materials is of great importance because results from the pilot study for this proposal (Study 1 in the preliminary studies section) indicated that this group could react to the intervention materials by drinking more. Although the results of Study 1 were not conclusive because of its post-test only design and the fact that this 'boomerang' effect in reaction to the materials was a trend rather than a statistically significant result, we feel that the study of these types of unintentional effects is essential. The personalized feedback pamphlet is intended for wide distribution in the general public. If we confirm that this ultra-brief intervention can have a negative impact on some sub-groups of problem drinkers then this finding would speak to the need to target the intervention to only those drinkers who already voice some concern regarding their drinking. As there is insufficient evidence to-date that could confirm or refute this hypothesis, we feel that the need to test this hypothesis appropriately outweighs the potential ethical dilemma of causing a small unintended increase in alcohol consumption among a population of drinkers who are not seeking treatment and who meet criteria for a rather liberal definition of problem drinking (AUDIT score of 8 or more).

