### Content of the Baseline Survey

(1) The Alcohol Use Disorders Identification Test will be used to measure level of alcohol consumption and severity of alcohol problems (a score of 8 or more on the AUDIT indicates a past 12 month alcohol problem) [64,65]. The AUDIT has been validated for use in telephone surveys [67]. Usual quantity of drinking will be assessed as a continuous variable. An additional item will ask the highest number of drinks the respondent recalled having on any one occasion in the past three months. Finally, respondents' drinking will also be assessed by asking the number of drinks consumed on each day of the last week.

(2) Six items assessing whether in the past 12 months alcohol had a harmful effect on respondents' (1) friendships/social life, (2) physical health, (3) outlook on life (happiness), (4) home life or marriage, (5) work, studies, or employment opportunities, or (6) financial position [68].

(3) Perceived drinking norms will be measured using a modified version of the Drinking Norms Rating Form [69]. Respondents will be asked how often they think a typical person their age and gender drinks and how often they consume five or more drinks on one occasion (same category response options as AUDIT). Further, respondents will be asked to estimate how much the typical person their age and gender usually drinks on one occasion.

(4) Perceived risk for drinking-related problems will be assessed using a six-item scale with questions about perceived vulnerability to harm from the drinkers' own perspectives [70].

(5) Following the procedure used by Neighbors [44], social reasons for drinking will be measured using the Social Rewards subscale of the Drinking Motives Questionnaire [63] a five item scale that asks respondents how often they are motivated to drink for positive social outcomes. Also, social outcomes expectancies and subjective evaluations of social effects of alcohol will be assessed using the sociability subscales of the Comprehensive Effects of Alcohol Scale [71].

(6) Formal addictions treatment utilization will be measured using a single item from the National Longitudinal Alcohol Epidemiological Survey [72]; "Have you ever gone anywhere or seen anyone for a reason that was related in any way to your drinking – a physician, counselor, Alcoholics Anonymous, or any other community agency or professional? Include help for combined alcohol and other drug use if alcohol was the major problem for which you sought help."

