(7) A series of demographic characteristics will be assessed: age, gender, ethnicity, marital status, education, and employment status.

Problem drinkers (AUDIT score of 8 or more) will be recruited to participate in a three-month and a six-month follow-up telephone survey.

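### The trial is described as being in drinkers not seeking treatment, but no entry rule screens for treatment, and the only baseline treatment item is lifetime, so recent help before randomisation goes unrecorded

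*Protocol article*

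**What the plan says.** The protocol article describes its population in two ways.

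- **Without a treatment restriction.** The section on the principal research objective sets out to "evaluate the efficacy of a pamphlet-based self-help intervention among problem drinkers in the general population". The Aim is to "evaluate the efficacy of a pamphlet-based personalized feedback intervention for problem drinkers in the general population". Hypotheses 1 and 2 speak only of respondents.
- **With one.** The Discussion says the primary goal is to "evaluate the efficacy of an ultra-brief self-help intervention for non-treatment seeking problem drinkers in the general population". The Rationale for the choice of study design, in weighing a possible small rise in drinking, refers to "a population of drinkers who are not seeking treatment and who meet criteria for a rather liberal definition of problem drinking".

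Entry, as set out under Design, Informed Consent Procedure and Content of the Baseline Survey, needs age 19 or older, drinking at least monthly, an AUDIT score of 8 or more and agreement to follow-up. The baseline section sums it up: "Problem drinkers (AUDIT score of 8 or more) will be recruited to participate in a three-month and a six-month follow-up telephone survey". All agreeing households are randomised. Treatment status plays no part.

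Baseline item (6) is the only treatment measure before randomisation. It begins "Have you ever gone anywhere or seen anyone for a reason that was related in any way to your drinking". At three and six months the same item is reworded to cover the last three months. The Abstract lists the impact on help seeking among the secondary hypotheses.

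**The concern.** Two things do not fit together.

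First, the label in the Discussion and the Rationale describes a population that the entry rules do not select. Someone now seeing a counsellor or attending a mutual-help group meets every stated criterion. A result reported under that label would claim more than the design supports, and one clause of the ethical argument would describe people whom the trial does not specifically enrol.

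Second, the baseline treatment item has a different recall window from its follow-up versions. A yes at baseline may mean last week or decades ago. A person already in treatment is likely to answer yes at follow-up in any arm, which adds help-seeking events that the pamphlet could not have caused. Without a dated baseline answer these events cannot be separated from new contacts. An analysis plan written later cannot repair this, because the information has to be collected before randomisation.

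**Working it through.** **1. Entry rules against the label.** Of the four criteria (age, monthly drinking, AUDIT score, agreement to follow-up), none refers to present or past treatment. The label is therefore not enforced. The entry rules do match the objective and the Aim.

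**2. What the baseline item can and cannot do.**

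- A no to the lifetime item rules out both current and past help, so a never-treated group can be defined before randomisation.
- A yes pools ongoing, recent and remote help, and nothing at baseline separates them.
- The three-month item is dated, but it is asked after randomisation. The personalized feedback pamphlet carries a referral telephone number, so the answer may be affected by the intervention and cannot stand in for baseline status.
- Other baseline measures are dated: the AUDIT problem definition and the six harm items refer to the past 12 months.

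**3. The plan's own figures.** Inputs from Power Analyses: f = 0.10 (1% of variance), power 80%, significance level .05 (two-sided assumed), 390 per condition. With f = 0.10, d = 2 × 0.10 = 0.20. The two-group formula gives 393 per arm. The F test at 1% of variance gives 779 in two arms, about 390 each. Recruitment is 1170 / 0.64 = 1828, stated as about 1830. These figures reproduce, and nothing here disputes them.

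**4. Illustration of size.** The Background gives an "estimated ratio of treated to untreated problem drinkers ranges from 1:3 to 1:14 in Canada and the United States". It does not say whether treated means currently or ever.

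- Treated share: 1/(1+3) = 25%; 1/(1+14) = 6.7%.
- Of 1830 recruited: 1830 × 0.25 = 458; 1830 / 15 = 122.

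If the ratio is lifetime, these are the people the existing item does identify, and those now in treatment are some unknown part of them.

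**5. Effect on the help-seeking comparison.** Let p be the share in treatment at baseline who would answer yes at follow-up in every arm, and q the rate of new contact among the rest.

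- Observed proportion in an arm: p + (1 − p)q.
- Difference between arms: (1 − p)(q₁ − q₀).

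The share p is expected to be equal across arms, so it cancels. The difference is not biased by imbalance, but it shrinks by the factor 1 − p and carries extra noise. Setting p to the whole treated share, as a ceiling, gives factors of 0.933 to 0.75. The true p is not given.

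**6. Precision of a subset analysis.** Removing the treated share from 390 per arm leaves 390 × (1 − 1/15) = 364, or 390 × 0.75 = 292.5. Power at d = 0.20 is about 77% and 68%, against about 80% in full. If the ratio is lifetime, this is the never-treated set, and a set without help in the past 12 months would be at least as large.

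**The case against.** The strongest reply is that the label is loose wording and not the target of inference. The objective, the Aim and the hypotheses are all set in general-population problem drinkers, and the entry rules match. The phrase can be read as contrasting a random-digit-dial sample with a clinic sample. Taking all problem drinkers also suits a trial that mimics a household mailing. This stands: the primary comparison is sound, and the formal objective needs no change.

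A reader might infer that people in treatment cannot be identified at all, so that the intended population is lost to analysis. The document does not support that. A no to the lifetime item marks the never-treated, and anyone now in treatment falls in the yes group. Only the split within the yes group is lost. A reader might also take 122 to 458 as the number in treatment at entry. The Background does not support that reading either, since it leaves the meaning of treated open.

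On help seeking, randomisation balances treatment already under way. The six-month survey also asks the personalized feedback arm whether they called the pamphlet's number. Balance removes bias but not dilution. The telephone question is put to one arm only and covers one route to help, so it does not replace a between-arm comparison.

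On ethics, the clause about treatment is one of several supports. The Rationale also cites the lack of existing evidence, what respondents are told and the liberal AUDIT threshold, and committee approval is stated. The point there is accuracy of description only.

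**Conclusion.** The point holds as an inconsistency in the population description together with a mismatched recall window. It is a cheap improvement, not a flaw in the primary comparison.

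The Discussion and the Rationale claim a population that the entry rules do not enforce. The document shows that people in treatment can be randomised, not how many will be. The baseline item separates never-treated from ever-treated but does not date the help, so the secondary help-seeking outcome lacks a matching baseline and its comparison is diluted.

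The size is uncertain. The only guide is the Background ratio, which rests on two assumptions: that it applies to this sample, and that its undefined term treated covers at least everyone now in treatment. On that footing the shrinkage of the help-seeking difference is at most 6.7% to 25%, and less if few are currently in treatment.

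**What to change.** - **Enrolment and Hypothesis 1:** leave both as they are, in the full randomised sample, and describe that sample in the wording of the principal research objective.
- **Baseline item (6):** keep the lifetime question. For those who answer yes, add whether any help was in the last three months, whether any was in the past 12 months, and whether it is ongoing.
- **Help-seeking analysis:** use this pre-randomisation answer, either by counting new contact among those without recent help or by adjusting for it.
- **Supportive analysis:** report Hypothesis 1 among those with no help in the past 12 months, as supportive only. Making it the headline would rest the main claim on a smaller set than the trial was sized for.
- **Wording:** bring the population statements in the Discussion and the Rationale for the choice of study design into line with the objective, the Aim and the Design section.

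The cost is one short extra question for a minority of respondents, one added subset analysis and some wording. The supportive estimate is less precise than the main one. Enrolment and sample size do not change.
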